# Intradermal acupuncture for rheumatoid arthritis: study protocol for a randomised controlled trial

**DOI:** 10.1186/s13063-021-05416-0

**Published:** 2021-07-14

**Keywords:** Rheumatoid arthritis, Intradermal acupuncture, Protocol, Randomised controlled trial

## Abstract

**Background:**

Rheumatoid arthritis (RA) is a common autoimmune disease that severely impacts quality of life. Currently available medications for the treatment of RA have adverse side effects. Emerging evidence suggests that intradermal acupuncture (IA) is feasible and safe for patients, but its application in RA patients has not been examined. Our study aims to explore the efficacy and safety of IA for the treatment of RA.

**Methods:**

This study is a randomised, sham-controlled, patient-outcome assessor-statistician blind trial that aims to evaluate the effects of IA in patients with RA. We will recruit 132 patients aged ≥ 18 years with a diagnosis of RA. Patients will be randomly allocated with a 1:1 ratio to IA or sham IA groups. Both groups will receive basic treatment and nursing routines for RA. The experimental group will receive actual IA treatment, whereas the control group will receive sham IA treatment. All patients will receive one course of treatment (i.e., four consecutive treatment sessions with an intervening 1-day interval). Primary outcomes will be traditional Chinese medicine (TCM) syndromes before and after a treatment course and Health Assessment Questionnaire (HAQ) scores. Secondary outcomes will be disease activity score 28 (DAS28) and levels of serum C-reactive protein (CRP). Outcome measures will be collected pre- and post-treatment.

**Discussion:**

This study aims to provide high-quality evidence for the efficacy and safety of IA for treating RA. In addition, the results will provide references for selection of acupoints for other syndromes in clinical practice.

**Trial registration:**

Chinese Clinical Trial Registry ChiCTR2000038028. Registered on 8 September 2020.

**Supplementary Information:**

The online version contains supplementary material available at 10.1186/s13063-021-05416-0.

## Background

Rheumatoid arthritis (RA) belongs to the category of “Wangbi” in Chinese medicine and is a common autoimmune disease associated with chronic synovial cell proliferation and inflammatory cell infiltration [1]. “Wangbi” is a disease caused by wind, cold, damp heat, and other external forces that block meridians and collateral joints, resulting in poor blood and qi movement. The main clinical manifestations include swelling, weightiness, and pain in joints throughout the body. This condition is characterised by joint pain, swelling, morning stiffness, and functional damage, which may lead to irreversible disability and significantly impact quality of life [2]. At present, curative treatments are lacking, and patients require treatment throughout life. In recent years, several clinical indications have suggested that the treatment of RA should be a combination of pharmacotherapy and comprehensive therapeutic modalities in order to achieve the best curative effects with minimal side effects [3–5].

Intradermal acupuncture (IA) is an approach that involves insertion of needles for a prolonged period. After a needle is buried under the skin, it can produce continuous and stable stimulation of the body and promote the effective operation of meridian qi and blood flow. Unlike conventional acupuncture, IA does not require lifting, pulling, or other actions and is therefore highly convenient.

IA has the advantage of providing patients with continuous stimulation and treatment without affecting daily activities, particularly for cases of chronic intractable pain. Moreover, this approach involves a combination of acupuncture and exercise therapy, which promotes qi and blood circulation, dredging meridians, and metabolism. As needles are restricted to the subcutaneous layer and do not penetrate the deep layer, the viscera, nerve trunk, and large blood vessels are preserved, and the technique is safe. IA causes minimal pain given that short needles are used [6]. Further, dizziness occurs less frequently in IA than in traditional acupuncture [7, 8]; hence, IA is more acceptable to patients.

Although IA is a new technology, there are still some other countries except China, such as Korea [9–11] and Japan [12], that have used IA treatment in the clinical practice. IA treatment is considered feasible and safe for patients with advanced cancer pain [9], post-stroke patients [6], and primary dysmenorrhea patients [13]. However, there is a paucity of reports on the application of IA in patients with RA. This study aims to investigate the clinical efficacy, adverse reactions, and safety of IA as a treatment for RA in order to promote clinical application of IA, accelerate disease rehabilitation, and improve patients’ quality of life.

## Methods/design

### Aim

The aim of this study will be to design a detailed research protocol for IA treatment for RA patients in China and to explore its clinical efficacy, adverse reactions, and safety.

### Study design

This is a two-arm, single-centre, randomised controlled trial conforming to the Standard Protocol Items: Recommendations for Interventional Trials (SPIRIT) guidelines (Additional file and Fig. 1). The process of participant inclusion is illustrated in Fig. 2.

**Fig. 1 Fig1:**
[figure not shown]
The schedules for patient enrollment, interventions, and assessments. **TCM**, traditional Chinese medicine; **HAQ**, Health Assessment Questionnaire; **DAS28**, disease activity score 28; **CRP**, C-reactive protein

**Fig. 2 Fig2:**
[figure not shown]
Flowchart of the study design

### Participants

Patients will be recruited by trained nurses from the Department of Rheumatology at a specific first-class hospital in Guangdong. More than 500 patients are admitted annually, ensuring that a sufficient number of clinical research cases can be included in the trial. All patients will undergo a general physical examination including electrocardiogram (ECG), chest film, routine blood work, examination of liver and kidney function, assessment of vital signs (body temperature, pulse, breathing, and blood pressure), examination of serum C-reactive protein (CRP) levels, coagulation function test, and disease activity score 28 (DAS28) prior to inclusion.

### Recruitment strategy

Patients will be recruited from the inpatient Department of Rheumatology at a specific first-class hospital in Guangdong from December 2020 to March 2022. Recruitment posters will be posted at the hospital. Two researchers will assess patient eligibility and provide study information, including study objectives, intervention measures, treatment time, benefits, and potential risks. Patients who agree to participate in this study will sign an informed consent form.

### Diagnostic criteria

The diagnostic criteria comprise Western and traditional Chinese medicine (TCM) diagnostic criteria. The Western diagnostic criteria are based on the 1987 American Rheumatology Association (ARA) revised RA classification criteria [14] and the 2009 American College of Rheumatology (ACR)/European League Against Rheumatism (EULAR) RA classification criteria [15]. TCM diagnostic criteria are based on the Chinese medicine industry standard of the People’s Republic of China (diagnostic criteria of TCM syndromes) (ZY/T001.1-94).

### Inclusion criteria

Patients will be included if they meet the following five criteria: (1) match the diagnostic criteria of RA, (2) meet the reference of “State Administration of TCM ‘Eleventh Five-Year’ key specialised cooperative group Wangbi (RA) diagnosis and treatment plan” syndrome indicative of liver and kidney deficiency, (3) DAS28 score of “mild” or “inactivity” with concomitant arthropathy in the extremities, (4) age ≥ 18 years, and (5) a signed informed consent form.

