### Outcomes

#### Primary outcomes

Primary outcomes are the evaluation of TCM syndromes before and after a course of treatment and Health Assessment Questionnaire (HAQ) scores.

TCM syndrome evaluation will be conducted according to the 2002 “Guiding Principles for Clinical Research of New Chinese Medicines [17]” based on the degree of joint pain; number of joints involved; joint swelling, tenderness, flexion, and extension; and other symptoms or signs. Scores will be divided into four levels: none, 0 points; light, 1 point; severe, 2 points; and very severe, 3 points. Four types of curative effects will be considered: (1) recovery: TCM syndrome scores decreased by ≥ 70%; (2) significant effect: TCM syndrome scores decreased by ≥ 50%; (3) effective: TCM syndrome scores decreased by ≥ 20%; and (4) ineffective: TCM syndrome scores decreased by less than 20%, whereby effectiveness rate = ([points before treatment – points after treatment]/points before treatment) × 100%.

HAQ scores will be used to assess patients’ physical function [18]. The HAQ is a widely used 20-item questionnaire that encompasses the following dimensions: dressing, washing, standing up, walking, and other aspects of daily life. Each question is scored on a scale from 0 to 3 points (0, no difficulty; 1, some difficulty; 2, very difficult; 3, unable to complete). The total score ranges from 0 to 60 points, and average scores range between 1 and 3 points. Higher scores indicate poorer health status.

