#### Secondary outcomes

Secondary outcomes are DAS28 and CRP levels. For DAS28, general health (GH), 28-joint swelling index (SJC), joint tenderness count (TJC), erythrocyte sedimentation rate (ESR), and visual analogue scale (VAS) scores will be evaluated. The 28 joints include the shoulder, elbow, wrist, metacarpophalangeal, proximal interphalangeal, and knee joints. The formula is as follows [19]:
$$ \mathrm{DAS}28-\mathrm{ESR}=0.56\times \sqrt{\left(\mathrm{TJC}28\right)}+0.28\times \sqrt{\left(\mathrm{SJC}28\right)}+0.70\times \ln \left(\mathrm{ESR}\right)+0.014\times \mathrm{GH}. $$

The level of disease activity will be categorised as follows: remission (≤2.6), low activity (>2.6 and ≤3.2), moderate activity (>3.2 and ≤5.1), and high activity (>5.1).

CRP is a non-specific marker of systemic inflammation that directly reflects the degree of inflammation and infection. CRP is widely used in clinical diagnosis and assessment of treatment efficacy for rheumatic and autoimmune diseases, especially during the active stage of the disease. Higher serum CRP levels indicate greater disease severity.

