### Data analysis

Data analysis will be performed using SPSS software (version 23.0; IBM SPSS Statistics, New York, USA) by statisticians independent of the research team.

Baseline data including age, sex, disease duration, evaluation of TCM syndromes, HAQ score, DAS28 score, and CRP values before interventions will be compared between the two groups. All analyses will be strictly conducted according to the intention-to-treat principle. Continuous variables such as age, disease course, and values of DAS28, HAQ, and CRP will be presented as mean ± standard deviation (SD). Categorical variables such as TCM syndromes will be presented as percentages. Student’s *t* tests will be used to compare quantitative data between the two groups. Data on adverse reactions will be analysed using the *X*^2^ test. Differences will be considered statistically significant at *P* < 0.05. Missing data will be imputed by multiple imputation. To assess the robustness of the results, a sensitivity analysis using a pattern-mixture model will be used.

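### CRP is set for an unadjusted t test on the raw scale, the HAQ average range contradicts its own scoring, and the DAS28 entry terms are not among the plan's DAS28 categories

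*Protocol article*

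**What the plan says.** **CRP.** Under Data analysis: "Continuous variables such as age, disease course, and values of DAS28, HAQ, and CRP will be presented as mean ± standard deviation (SD"). Quantitative data are to be compared between groups by Student's t test. No transformation or baseline adjustment is named, although CRP is measured before and after treatment. Under Secondary outcomes, CRP is described as widely used in rheumatic disease, "especially during the active stage of the disease".

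**HAQ.** Under Primary outcomes: "The HAQ is a widely used 20-item questionnaire"; "Each question is scored on a scale from 0 to 3 points"; and then "The total score ranges from 0 to 60 points, and average scores range between 1 and 3 points". The section does not say whether the total or the average is analysed.

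**DAS28.** Inclusion criterion 3 requires a "DAS28 score of “mild” or “inactivity” with concomitant arthropathy in the extremities", with no cut-off. Secondary outcomes gives the DAS28-ESR formula and these categories: "remission (≤2.6), low activity (>2.6 and ≤3.2), moderate activity (>3.2 and ≤5.1), and high activity (>5.1"). The Discussion refers to DAS28-CRP instead.

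**The concern.** CRP is a concentration that cannot be negative, and such measures often have a long right tail. A mean ± SD then describes the typical patient poorly, and a t test on raw values lets a few high readings dominate the variance. The baseline CRP that the trial already collects is left out of the comparison.

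The HAQ problem sits on a primary outcome: the stated average range cannot be derived from the stated items and total. The DAS28 problem sits on eligibility. Two researchers assess eligibility against words that the plan does not define, so the enrolled population is not reproducible from the text. How far DAS28 can improve also depends on what those words mean.

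**Working it through.** **1. The plan's sample size, which supplies the group size used below.** Inputs from Power calculation: rates of 95% and 78%, two-sided alpha 0.05, power 0.80.

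n = (1.960 + 0.842)² × [0.95 × 0.05 + 0.78 × 0.22] / (0.95 − 0.78)² = 7.849 × 0.2191 / 0.0289 = 59.5, so 60 per group.

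The plan's figure is reproduced. It rests on a response rate, so nothing below changes it.

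**2. CRP.** The document gives no mean, SD or shape for CRP, so the distribution is an assumption: log-normal, 60 per group, 20,000 simulated trials per setting. The true difference is 0.51 log-SD, close to the difference that gives 80% power on the log scale: (1.960 + 0.842) × √(2/60) = 0.51.

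| Assumed log-SD | Power, raw t test | Power, log-scale t test |
|---|---|---|
| 0.8 | 67% | about 79% |
| 1.0 | 60% | about 79% |
| 1.2 | 53% | about 79% |

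With no true difference, the raw test rejected in 4.9%, 4.6% and 3.6% of trials at log-SD 0.6, 1.0 and 1.3. It is therefore valid but inefficient. The table covers the change of scale only. Adjusting for baseline would add a gain that depends on the correlation between baseline and post-treatment log CRP, which the document does not give.

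**3. HAQ.**
- Total: 20 × 0 = 0 to 20 × 3 = 60, which agrees with the plan.
- Average: 0/20 = 0 to 60/20 = 3, against the stated 1 to 3.
- An average of 1 is a total of 1 × 20 = 20, so totals of 0 to 19 are valid on the total scale but outside the stated average range.

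**4. DAS28.** The entry terms are 'mild' and 'inactivity'. The defined categories are remission, low, moderate and high. Neither entry term is among them.

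Suppose 'mild' means low activity and 'inactivity' means remission. Entry is then capped at 3.2. In the plan's formula the ESR term is 0.70 × ln(ESR). With ESR unchanged, the largest possible fall comes with no tender joints, no swollen joints and general health of 0, and equals the entry score minus the ESR term.

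| Assumed ESR | ESR term | Largest fall from 3.2 | Largest fall from 2.6 |
|---|---|---|---|
| 10 | 1.61 | 1.59 | 0.99 |
| 20 | 2.10 | 1.10 | 0.50 |

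If ESR itself fell from 20 to 10, the score would drop a further 0.70 × ln(2) = 0.49.

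**The case against.** **CRP.** Skewness and every log-SD are assumed, and setting the effect on the log scale favours the log test. Type I error is not harmed, CRP is secondary, and an analysis plan not shown here could name a transformation. All of that is fair and limits the point to efficiency. It does not remove it: the article does not leave the method open but states both the summary and the test.

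**HAQ.** The item range and the total are right, and no analysis is tied to the wrong bound. A reader might infer that valid low scores would be rejected at data entry. The document describes no range check of 1 to 3, so that consequence is not supported. The misstated scale remains.

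**DAS28.** The cap of 3.2 depends on an assumed reading of undefined terms, and holding ESR fixed understates the room, since ESR is part of the outcome. Both stand, so the headroom figures are conditional. A reader might also infer from the screening list, which names CRP but not ESR, that ESR is missing before inclusion. That does not follow: Participants lists DAS28 itself and routine blood work among the assessments before inclusion, and the only formula given requires ESR.

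**A common floor.** A reader might infer that HAQ, DAS28 and CRP all start near their floor. The document gives no baseline values. The entry limit is on DAS28, not on function; patients are inpatients with required arthropathy of the extremities, so HAQ may well be raised. CRP is not a term in DAS28-ESR, so no CRP ceiling follows. The remark about CRP in active disease is a reason for caution, not evidence of a floor.

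**Conclusion.** Three points hold, each modest.

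- **CRP:** the stated analysis is valid but probably inefficient. Under log-normality with log-SD 0.8 to 1.2 and 60 per group, power is about 67% to 53% against about 79% on the log scale. This rests on assumed skewness.
- **HAQ:** the average range is wrong by the plan's own scoring. It is 0 to 3. No assumption is needed.
- **DAS28:** the entry terms and the categories do not match and must be reconciled. If the terms mean low activity and remission, the largest fall from 3.2 is about 1.1 points at an unchanged ESR of 20 and 1.6 at ESR 10.

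On that reading a null result on DAS28 could partly reflect limited room. It would be too strong to say that a null on DAS28 or CRP would show the floor rather than the treatment: it could equally mean no effect, and no floor is shown for CRP or HAQ. The sample size is unaffected.

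**What to change.** 1. **CRP:** analyse post-treatment log CRP by a linear model with treatment group and baseline log CRP, and report the ratio of geometric means with its confidence interval. This uses data already collected. The small cost is a change of summary measure, from a difference in means to a ratio.
2. **HAQ:** correct the average range to 0 to 3 and name the total (0 to 60) as the analysed score. This is a wording change.
3. **DAS28:** the sponsor should state which of the plan's own categories and cut-offs criterion 3 was meant to refer to, and use one DAS28 formula at screening, baseline and after treatment. Which categories were intended is for the sponsor to say. Because recruitment is under way, the clarification should record how the criterion has been applied so far.

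DAS28 and CRP should not be recast as no-worsening outcomes. That would change the question they answer, and the plan has no margin for it.

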### Exclusion criteria

Patients will be excluded if they meet any of the following criteria: (1) present with comorbid diseases, including severe cardiopulmonary disease, liver or kidney disease, coronary heart disease, diabetes, blood diseases, or malignant tumours; (2) pregnant or lactating women; (3) fever or clotting disorder; (4) receiving treatment for local skin ulcers or skin diseases; (5) allergic constitution and allergies to adhesive tape; and (6) participation in any other clinical trials.

### Power calculation

Sample size was determined based on the formula for sample size calculation comparing two groups with independent sampling rates:
$$ \mathrm{n}1=\mathrm{n}2=\frac{{\left({Z}_{1-\alpha /2}+{Z}_{1-\beta}\right)}^2\left[{P}_1\left(1-{p}_1\right)+{P}_2\left(1-{p}_2\right)\right]}{{\left({p}_1-{p}_2\right)}^2} $$

Based on previous clinical research, the rate for the trial group that received IA for RA treatment was 95% and that of the control group was 78% [16]. In this study, assuming *α* = 0.05 (both sides) and 1 − *β* = 0.80, the required sample size was calculated as 60 per group. Considering a dropout rate of 10%, we concluded that the required sample size was 66 per group. Therefore, a total of 132 patients with RA will be recruited.

### Randomisation

RA patients who meet the inclusion criteria and agree to participate in this research will be randomly allocated to either the intervention group or control group, with an allocation ratio of 1:1. The random allocation sequence will be generated by a statistician (not involved in the study) using a computer programme. Each random number with a group assignment will be written on a piece of paper and inserted into a sealed envelope. Following baseline assessment, participants will be provided with an envelope according to the randomisation sequence.

### Blinding

Blinding IA operators in acupuncture clinical trials is challenging. However, it is feasible to conceal patient and group assignments from outcome assessors and statisticians. Patients will be informed that they will receive one of two effective IA interventions after enrolment. During the IA treatment, patients in different groups will be treated in separate rooms to avoid communication. At the end of follow-up, the patients will be asked to guess which treatment they were receiving to determine the credibility of blinding. Outcome assessors and statisticians will be blinded to group allocations. Blinding will be disclosed only when it must be known whether a patient is receiving intradermal acupuncture treatment or sham acupuncture treatment in order to manage a serious adverse event.

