### Control intervention

RA patients will receive basic treatment and nursing routines. Basic treatment will comprise oral celecoxib, leflunomide, and methotrexate. Routine nursing measures will encompass lifestyle, diet, medication, psychology, and exercise. Patients will be required to remain vigilant regarding joint warmth and avoid cold stimulation and/or long-term weight-bearing of small joints. Patients will be encouraged to adopt a healthy diet and lifestyle by prioritising nutritious low-salt and low-fat foods, abstaining from fried or spicy food, and quitting smoking and alcohol. Nursing staff will introduce commonly used drugs, basic medication methods, and basic pharmacological effects of clinical drugs to improve patients’ understanding of their daily medication. Patients will be encouraged to stay positive and maintain social interactions. Patients will be encouraged to perform slow or fast walking, square dancing, joint exercises, and other activities, as desired.

The aforementioned intervention acupoints will be treated with pseudo-intradermal needling (placebo). No needles will be present under the adhesive tape of the sham treatment group; the tape will merely be adhered to the surface of acupoints. Patients will be required to press the needle embedding points for 1 to 2 min every 3 to 4 h to simulate an increase in stimulation and efficacy.

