### Adherence improvement

Before the participants are enrolled in the study, our researchers will inform the patient of the study information, including study objectives, intervention measures, treatment time, benefits, and potential risks. These lay the foundation for patient compliance. During the intervention period, our researchers will instruct patients to press the needle embedding points for 1 to 2 min every 3 to 4 h to simulate an increase in stimulation and efficacy. Two team members will also inspect measurements during progress for monitoring adherence. The data monitoring committee will also inspect data is adequately recorded in the CRFs. If patients suffer an adverse event, our rheumatologists and first-line physicians will respond to emergencies in a timely manner and provide free medical guidance. After all follow-ups, we will provide 3 months of free intradermal acupuncture for patients in the sham group. All treatment and examination costs in this study are free and borne by the team. Certain transportation subsidies will also be provided. These will contribute to improving adherence.

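### Patients are to be told that both treatments are effective intradermal acupuncture, although one is placebo tape without a needle, and this message conflicts with the post-trial offer to the sham group

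*Protocol article*

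**What the plan says.** Four sections of the protocol article bear on what patients know about their treatment.

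- **Blinding:** "Patients will be informed that they will receive one of two effective IA interventions after enrolment". The same section plans a check at the end of follow-up, when "the patients will be asked to guess which treatment they were receiving to determine the credibility of blinding".
- **Control intervention:** the control procedure is labelled a placebo and is described as follows: "No needles will be present under the adhesive tape of the sham treatment group; the tape will merely be adhered to the surface of acupoints".
- **Recruitment strategy:** before consent, two researchers assess eligibility and "provide study information, including study objectives, intervention measures, treatment time, benefits, and potential risks". The Adherence improvement section repeats that this information is given before enrolment.
- **Adherence improvement:** "After all follow-ups, we will provide 3 months of free intradermal acupuncture for patients in the sham group". After this and some other benefits (free treatment and examinations, transport subsidies), the section concludes: "These will contribute to improving adherence".

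The Abstract describes the trial as sham-controlled and as blinded for patients, outcome assessors and statisticians.

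**The concern.** The message in the Blinding section and the description of the control cannot both be accurate. The adherence plan then adds a benefit defined by membership of the sham group, which is an arm that the message implies does not exist.

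This matters for three reasons. Patient blinding is one of the trial's headline design claims. Both primary outcomes depend largely on what patients report: the HAQ is a questionnaire on physical function, and the TCM syndrome score draws on joint pain and other symptoms. And the treatment guess is the only check on patient blinding that the article describes. A guess is easier to interpret if it is known what the patient had been told about the possible treatments.

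**Working it through.** The plan gives no figure on this point, so the check is a comparison of statements.

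**Step 1. Is the message true of the control arm?** The message makes two claims about each arm: that it is IA, and that it is effective. The Control intervention section says the control is tape on the skin with no needle, and labels it placebo. On the protocol's own description the control is not IA, and nothing in the article claims that it is effective. Both parts of the message fail for the control arm. This holds whether the words about enrolment describe when patients are told or when they are treated.

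**Step 2. Is the message secure for the IA arm?** Here the article is mixed. The Abstract says IA has not been examined in RA and the Background notes few reports, while the Power calculation cites earlier research with a 95% rate for IA in RA. The Aim treats efficacy as the question to be explored. The conclusion does not need this step; Step 1 is enough.

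**Step 3. Does the message fit the post-trial offer?** The time at which patients hear of the offer is not stated. There are two cases for an offer worded as the article words it.

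| Offer to the sham group disclosed | Effect on the blinding message | Effect on adherence |
|---|---|---|
| Before or during treatment | Contradicted: patients learn that one arm is a sham | The offer can act as an incentive |
| Only after all follow-ups | Not contradicted during the trial | The offer cannot have influenced adherence |

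In the first case the Blinding section is contradicted. In the second, the closing statement of the Adherence improvement section is wrong as regards this offer. The two sections therefore conflict as written.

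**Step 4. Does the information given before consent settle it?** The article says that the intervention measures are explained, but not how the control is described. The consent pages are not available, so their wording cannot be checked. Whatever they say, the Blinding section still fixes a message that the Control intervention section contradicts.

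**The case against.** The strongest reply is that the harm is unproven. The article does not say when or in what words the offer is made. The adherence sentence closes a list that contains several other benefits and may be no more than loosely worded. If the offer is disclosed only after follow-up, patient blinding is untouched. An arm-neutral wording could also support adherence without exposing the sham. Giving both arms the same expectation is what a sham control is for. All of this stands, and it limits the point to inconsistency. It does not make the message true.

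Three stronger readings are tempting, and the documents support none of them.

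- **That the blinding defeats itself.** A reader might infer this from the sham-group offer. But knowing that a sham exists does not tell a patient which arm they are in, and the timing of disclosure is unstated.
- **That patients can find out by pressing the site.** Both arms press the points, but nothing says that a patient can feel whether a 1.2-mm needle is present.
- **That raised expectancy in the sham arm costs power.** With the planned 60 per group and power = Φ(|p1 − p2| / √{[p1(1 − p1) + p2(1 − p2)]/60} − 1.96), the planned 95% v 78% gives 0.803, and an assumed 95% v 80% gives 0.723. That comparison raises expectancy in one arm only, although both arms hear the same message. If both rise by two points, 97% v 80% gives 0.857. No document gives an expectancy effect, so neither the direction nor the size of any change in power can be derived.

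**Conclusion.** The point holds as a contradiction in the text. The message in the Blinding section is untrue, because the control is needle-free tape that the protocol itself calls placebo. It also conflicts with the Adherence improvement section over the offer to the sham group.

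The first conclusion rests only on the article's own sentences. The second rests on one further premise: that an offer can improve adherence during the trial only if patients know of it, and that it is made in the sham-group terms in which the article states it.

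No numerical size can be given. Whether unblinding occurs, and in which direction any bias would run, cannot be settled from the documents: higher expectancy in the sham arm alone would shrink the contrast, while unblinding would tend to inflate it. The correction should be made because it is cheap and makes the patient information and the blinding check coherent. The sample size and analysis are unaffected.

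**What to change.** 1. In the Blinding section, delete the word effective. Use one accurate, neutral script for every patient, identical at consent and after enrolment: allocation by chance to one of two forms of intradermal patch treatment, one of which is a sham. It should say is, not may be, because the protocol calls the control a placebo.
2. In the Adherence improvement section, describe the post-trial offer in arm-neutral wording and state when patients are told of it.
3. Match the response options of the treatment-guess question to that script.
4. The Trial status section puts the first enrolment at 15 December 2020, so a new script reaches only the remaining patients. Record and report which script each patient received, and show the treatment guesses by script.

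Cost: rewording of the patient information and an ethics notification. Expectancy may be slightly lower under the accurate script, and earlier and later patients will have heard different messages, which is why item 4 is needed.
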